**Blood pressure measurement**

Following the blood pressure measurement protocol in 2017 AHA’s hypertension guideline, participants are required to abstain from alcohol, caffeine, smoking and exercise for at least 30 minutes before measurement. Blood pressure and heart rate are measured in a seated position following bladder voiding and 10 minutes of resting in quiet, temperature-controlled room^(2)^. We use Nissei DM-3000 automated digital blood pressure monitor with appropriate cuff size placed on the arm they have chosen for procedure. They are measured for 3 times with 2 minutes interval between each measurement and the average value is used for analysis. To control diurnal variation of blood pressure and medication intake cycle, measurement at baseline and post-procedure are done approximately at the same time of day. The time of ingesting antihypertensive medication is standardized.

**Grip strength measurement**

Grip strength measurement is conducted in the same position as exercise position. Subjects held Jamar plus+ digital hand dynamometer with their preferred hand and conduct a maximum voluntary contraction in seated position, shoulders adducted and neutrally rotated, elbow flexed at 90°, forearm in neutral and wrist between 0 and 30° of dorsiflexion. Three trials are taken at 1min intervals. The mean of three trials is used for analysis^(21)^.

**Questionnaire**

Satisfaction of the exercise is rated in Likert scale, providing quantitative data. Questions asking if participants would continue to perform this exercise after the study, any comments and complications regarding exercise are pursued in descriptive data.

**Sample size calculation**

A sample size of 36 participants (18 patients per group) is calculated based on mean difference and SD from Millar PJ et al. study in 2008^(13)^ with 5% error and 90% power.

Formular n/group = 2(Zα/2 + Zβ)2 σ2 / (X1-X2)2

where σ2 = [(n1-1) S12+(n2-1)S22] / (n1+ n2 - 2)]

X1-X2 = (-10) – (-1) = 9, SD1 = 8.98, SD2 = 2.36, n1 = 24, n2 = 25

α = 0.05, β = 0.10, Zα/2 = 1.96. Zβ = 0.84

n/group ~ 12

Since home-based protocol is susceptible to higher dropout rate, we estimate 30% of dropout rate and calculate total n/group = 18

**Statistical analysis**

Statistical analyses are performed using SPSS Statistics Version 22. Demographic data are analyzed and present as mean, SD and percent. Within group comparison is used to analyze pre-post treatment using paired T-test. Between-group comparison is used to analyze mean difference between group using unpaired T-test if baseline characteristics are similar, or ANCOVA if baseline characteristics are different. All statistical tests are two-tailed, statistical significance is set at p<0.05, and using intention to treat analysis.

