**Literature review**

In 2014, an anchor systematic review and meta-analysis by Debra J. Carlson et al has revealed the effectiveness of isometric resistance training lasting 4 or more weeks in lowering systolic blood pressure (SBP) by -6.77mmHg(95%CI -7.93,-5.62;P<0.001), diastolic blood pressure (DBP) by -3.96mmHg(95%CI -4.80,-3.12;P<0.001), and mean arterial pressure (MAP) by -3.94mmHg(95%CI -4.73,-3.16;P<0.001), respectively^(5)^. Another systematic review and meta-analysis in 2015 by Jodie D Inder et al reported a subgroup analysis that anti-hypertensive effects is larger in hypertensive male aged ≥45years, using unilateral arm isometric resistive training conducting for at least 8 weeks^(6)^. These two systematic reviews, which were cited in 2017 AHA’s hypertension guideline, retrieved data from common RCTs regarding isometric resistance exercise with different characteristics: unilateral/bilateral/alternating isometric handgrip contraction, double leg extension exercise.

In 2018, K.F. Goessler et al conducted a home-based randomized controlled trial using telemonitoring and telecoaching to compare BP response in isometric handgrip exercise versus moderate intensity aerobic exercise in healthy adults. Trial was 8 weeks duration with handgrip group performing daily, while aerobic group performing moderate intensity aerobic exercise for at least 150 minutes per week. The result showed a significant reduction in both ambulatory and office DBP in aerobic group, but significant reduction in only office SBP in handgrip group. They concluded that aerobic exercise should remain a number one recommendation in the prevention and treatment of hypertension, while isometric handgrip exercise could be a useful tool for lowing blood pressure in elderly adult or patients who have multiple comorbidities.^(18)^

There was a RCT in 2002 conducting an isometric handgrip exercise in hypertensive elderly population, aging 60-80 years old, and revealed significant hypotensive effect following 10 weeks of standard 4sets of 2minutes handgrip exercise at 30% MVC, 3 days per week. SBP was reduced from 156±9.4 to 137±7.8 mmHg in exercise group versus 152±7.8 to 144±11.8 mmHg in non-exercise group. 75% of the hypertensive elderly participants had been taking antihypertensive medication for many years.^(10)^

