**Expected benefits gain**

If our protocol for home-based isometric exercise using commercial available device could result in blood pressure reduction in hypertensive elderly adults, it would be an alternative or add-on exercise that can help in blood pressure management in patients who are unable to perform aerobic exercise.

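### The plan tests pre-post change within arms at the same p<0.05 as the between-group test and does not say that the between-group test alone decides effectiveness

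*Protocol*

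**What the plan says.** The protocol's Statistical analysis section prescribes two kinds of comparison. The first is within arm: "Within group comparison is used to analyze pre-post treatment using paired T-test". The second is between arms: "Between-group comparison is used to analyze mean difference between group using unpaired T-test if baseline characteristics are similar", with ANCOVA if baseline characteristics differ. One rule then covers both: "All statistical tests are two-tailed, statistical significance is set at p<0.05". The section does not call the paired tests descriptive, and it does not name the between-group test as the one on which effectiveness is judged.

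The Sample size calculation section does point to the between-group difference. Its inputs are "X1-X2 = (-10) – (-1) = 9, SD1 = 8.98, SD2 = 2.36, n1 = 24, n2 = 25", "with 5% error and 90% power".

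The protocol reports control-arm SBP change from two cited trials. In the Literature review, a 10-week trial in hypertensive people aged 60-80 gives "SBP was reduced from 156±9.4 to 137±7.8 mmHg in exercise group versus 152±7.8 to 144±11.8 mmHg in non-exercise group". In the sample size inputs, the normotensive 2008 study has a control change of -1 mmHg.

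**The concern.** A paired test in the exercise arm asks whether SBP changed over 8 weeks. It does not ask whether exercise changed it. Anything that moves SBP in both arms, such as getting used to repeated measurement or the attention of being in a trial, enters the paired test in full and cancels only in the between-group comparison.

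Because both tests have the same formal standing, a report could cite a significant fall in the exercise arm, or a significant fall there with none in control, as evidence of efficacy when the randomised difference shows nothing. In a trial with about 12 completers per arm, the p-values of the two arms can easily fall on opposite sides of 0.05 by chance.

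**Working it through.** **1. The plan's own figure.** The sample size inputs give a pooled variance of (23 × 8.98² + 24 × 2.36²)/47 = (1854.73 + 133.67)/47 = 42.31, so SD = 6.50. At 90% power, n per group = 2 × (1.96 + 1.2816)² × 42.31/9² = 10.98, so 11. The plan states about 12, and a t-based calculation at 12 per group gives 89.9% power, so the figure is in line with 90% power. (The printed Zβ of 0.84 would give 8.2, so 9. That is a separate inconsistency and does not affect this point.) With 30% dropout, 12/0.7 = 17.1, so 18. The trial is therefore sized on a difference between arms of 9 mmHg, not on a change within an arm.

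**2. Background change in the cited trials.**
- Elderly hypertensive trial: controls 152 - 144 = 8 mmHg; exercise 156 - 137 = 19 mmHg; difference 11 mmHg. The controls' fall is 8/19, about 42%, of the exercise arm's fall.
- Normotensive 2008 study: controls 1 mmHg; exercise 10 mmHg; difference 9 mmHg.

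**3. What a paired test would make of the 8 mmHg control fall.** The SD of change is not given. From SDs 7.8 and 11.8 and an assumed pre-post correlation r, SD = √(7.8² + 11.8² - 2r × 7.8 × 11.8), and t = 8/(SD/√n).

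| r (assumed) | SD of change | p, n=12 | p, n=18 |
|---|---|---|---|
| 0 | 14.1 | 0.076 | 0.028 |
| 0.5 | 10.4 | 0.022 | 0.005 |
| 0.7 | 8.4 | 0.007 | 0.001 |

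In a group of this trial's size, a fall like that in people who did not exercise would be significant at 0.05 in every case except r = 0 with n = 12.

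**4. How often the exercise-arm paired test misleads.** Assume no exercise effect and the same true fall d in both arms. Take the SD of change as 8.98 (the larger SD in the sample size inputs, read as an SD of change) up to an assumed 12. The probability of a significant fall comes from the noncentral t distribution with n - 1 degrees of freedom and noncentrality d√n/SD. For example, d = 8, SD = 8.98 and n = 12 give a noncentrality of 3.09 and a probability of 0.80.

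| Common fall d | SD 8.98, n=12 | SD 12, n=12 | SD 8.98, n=18 | SD 12, n=18 |
|---|---|---|---|---|
| 1 mmHg | 5.4% | 4.5% | 6.5% | 5.2% |
| 4 mmHg | 29% | 18% | 43% | 27% |
| 6 mmHg | 56% | 35% | 76% | 52% |
| 8 mmHg | 80% | 56% | 95% | 76% |

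The between-group t-test keeps its 5% two-sided error whatever d is (simulated at 4.8% to 5.1%), so it wrongly favours exercise in 2.5%.

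**5. Significant in exercise, not in control.** With independent arms this has probability p(1 - p), where p is the single-arm probability above. At d = 4 to 6 mmHg and n = 12 it is 21-25% for SD 8.98 and 15-23% for SD 12.

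**The case against.** The strongest reply is that the between-group test is already the main one in substance. The design is randomised and controlled, the sample size is built on the difference between arms, the between-group test is planned, and no section says that a paired test would show efficacy. Listing the paired test first does not rank it first, and ranking tests is often left to an analysis plan. Most of this stands. A reader might infer that the plan judges efficacy within one arm and discards its control group; the documents do not support that. What remains is that the protocol itself prescribes the paired significance tests and gives them the same threshold with no statement of role.

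Three further readings go too far.
- The Expected benefits gain section speaks of whether the exercise "could result in blood pressure reduction in hypertensive elderly adults". A reader might take this as a success criterion that one arm's fall could meet. It is a conditional sentence about clinical usefulness and defines no test.
- A reader might add regression to the mean as a source of falling SBP. The entry criteria set no SBP floor and exclude 160 mmHg or more, so selection gives no downward regression. Nor is the standardised medication timing shown to lower SBP; the protocol presents it as a control on variation.
- A reader might take 8 mmHg as the expected drift. It comes from one of two cited control groups, whose mean SBP started at 152 mmHg. At the other group's 1 mmHg, with SD 8.98 to 12, the false signal is about 5% at 12 per arm. With that control group's own SD of 2.36 it would be 27%.

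**Conclusion.** The point holds as a matter of wording that should be fixed. The right test is planned and the trial is sized for it, but nothing in the protocol makes it decide, and a second prescribed test at the same threshold can mislead. With no exercise effect and 12 per arm, the false signal is about 5% at a 1 mmHg common fall, 18-56% at 4-6 mmHg and 56-80% at 8 mmHg, against 2.5% for the between-group test in the same direction.

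These figures assume normally distributed changes, an equal true fall in both arms and an SD of change between 8.98 and 12. The 4-6 mmHg range is an assumption lying between the two cited control falls. How far SBP will drift in this trial is unknown, which is the reason to let the control arm decide.

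It would be too strong to say that a pre-post fall carries no information about the exercise. It does not by itself separate exercise from background change.

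**What to change.** In the Statistical analysis section, state that effectiveness is judged only on the between-group difference in week-8 resting SBP, adjusted for baseline SBP by ANCOVA, with its 95% CI. State that within-arm changes are reported descriptively, as means with SD or CI, without p-values.

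This uses data already planned for collection at both visits and needs no more participants. The only cost is fewer p-values in the report.

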**Outcome measurement**

Baseline blood pressure, grip strength and skeleton muscle mass (SMM) are measured at the first visit. After 8 weeks, all participants are appointed at clinic to assess blood pressure, grip strength and SMM. We use InBody 770 body composition and body water analyzer to measure SMM. Thai short IPAQ is used to assess the physical activity level at both visits^(21)^. Questionnaire is given concerning the satisfaction of this exercise and any possible post-procedural musculoskeletal side effect. Blood pressure, grip strength and SMM are measured by the same research member who is blinded to randomization and treatment procedure.

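### Choosing a t-test or ANCOVA from the observed baseline gives up precision and leaves chance imbalance in baseline SBP unadjusted; baseline-adjusted ANCOVA should be used in every case

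*Protocol*

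**What the plan says.** The protocol's *Statistical analysis* section gives one rule for comparing the groups: "unpaired T-test if baseline characteristics are similar, or ANCOVA if baseline characteristics are different". It adds: "All statistical tests are two-tailed, statistical significance is set at p<0.05, and using intention to treat analysis". It does not say how similarity is judged. Nor does it state outright whether the t-test is on change from baseline or on the week-8 value; the sample size is built on the difference in mean change.

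The covariate that matters is already collected. Under *Outcome measurement*: "Baseline blood pressure, grip strength and skeleton muscle mass (SMM) are measured at the first visit". *Study design* describes blocked randomization and mentions no stratification, so only chance balances baseline SBP.

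**The concern.** In a randomised trial, the case for adjusting for the baseline value of the outcome does not depend on whether the arms look different. It rests on the correlation between baseline and follow-up, which exists either way. A rule that adjusts only after a visible imbalance has two costs.

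- **Conditional shift.** With 18 per arm or fewer, a baseline gap of several mmHg can easily pass as similar. Part of that gap then stays in the treatment estimate.
- **Lost precision.** In most trials run under the rule the plain t-test is used, and the variance explained by baseline SBP is left in the error term.

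At stake is the main between-group comparison of a small trial planned on 12 evaluable participants per arm.

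**Working it through.** **Inputs from the protocol**
- *Sample size calculation*: "X1-X2 = (-10) – (-1) = 9, SD1 = 8.98, SD2 = 2.36, n1 = 24, n2 = 25"; "with 5% error and 90% power"; "we estimate 30% of dropout rate and calculate total n/group = 18".
- *Literature review*, the cited RCT in hypertensive elderly people: baseline SBP 156±9.4 and 152±7.8 mmHg. The ± is read as an SD (assumption).
- *Introduction*: a guideline effect of about 5 mmHg in hypertensive patients, used as a smaller effect.

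**Assumptions not in the protocol**
- Correlation ρ between baseline and week-8 SBP: 0.3 to 0.8.
- Similar means p>0.05 on a baseline SBP t-test.
- Equal SDs at both visits and in both arms for the power runs.

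**1. The plan's own figure.** Pooled variance = (23×8.98² + 24×2.36²)/47 = 42.3, so the SD is 6.50. At 90% power, n = 2×(1.96+1.28)²×42.3/81 ≈ 11 per arm. The t-based calculation gives 12 (power 0.899). Dropout: 12/0.7 = 17.1, rounded up to 18. The stated 12 and 18 are reproduced. (The line "α = 0.05, β = 0.10, Zα/2 = 1.96. Zβ = 0.84" prints the z-value for 80% power, which would give 8.2, i.e. 9 per arm. That is a separate slip.)

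**2. Gap that passes as similar, 18 per arm.** Limit = t(0.975, 34)×SD×√(2/18), with t = 2.032.
- SD 7.8: 2.032×7.8×0.333 = 5.3 mmHg.
- SD 9.4: 2.032×9.4×0.333 = 6.4 mmHg.

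**3. Shift left in a change-score estimate** = (1−ρ)×gap.
- At the limit, ρ = 0.5: 2.6 to 3.2 mmHg. At ρ = 0.3 it is 3.7 to 4.5; at ρ = 0.8 it is 1.1 to 1.3.
- Typical case: the median absolute gap is 0.674×SD×0.333 = 1.8 to 2.1 mmHg, which at ρ = 0.5 shifts the estimate by 0.9 to 1.1 mmHg.

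**4. Illustration from the cited RCT.** SBP went from 156 to 137 against 152 to 144, a baseline gap of 4 mmHg, which is below the limits in step 2. The change comparison gives 19−8 = 11 mmHg and the follow-up comparison 144−137 = 7 mmHg. ANCOVA with an assumed slope of 0.5 gives 7+0.5×4 = 9 mmHg.

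**5. Power, 12 per arm, change SD held at 6.50.** The ANCOVA residual variance is S²(1−ρ²) and the change variance 2S²(1−ρ), a ratio of (1+ρ)/2. Simulated power, with the t-test on change scores:

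| ρ | Variance ratio | Rule, 9 mmHg | ANCOVA, 9 mmHg | Rule, 5 mmHg | ANCOVA, 5 mmHg |
|---|---|---|---|---|---|
| 0.3 | 0.65 | 91% | 97% | 44% | 59% |
| 0.5 | 0.75 | 90% | 95% | 43% | 53% |
| 0.7 | 0.85 | 90% | 93% | 43% | 48% |
| 0.8 | 0.90 | 90% | 91% | 43% | 46% |

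Repeat simulations agree to within about one percentage point. The rule recovers almost none of the loss, because under randomisation a p>0.05 check passes in 95% of trials and the t-test is then used. If the t-test were on week-8 values, the rule's power at 9 mmHg would be 97%, 91%, 72% and 55% at these four correlations.

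**6. Type I error, 12 per arm.** A fixed p>0.05 rule with change scores gives 4.1% to 4.8%; ANCOVA gives 5.0%.

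**The case against.** The strongest reply is that the harm is modest, and much of it stands.

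- **Validity.** A reader might infer that a two-stage rule inflates the false-positive rate. A fixed rule does not; it is slightly conservative. Rates of about 6% to 9% arise only if the analyst picks between tests after seeing the outcome results. The protocol ties the choice to baseline characteristics and does not say it would be made that way.
- **Bias.** Averaged over randomisations, the t-test estimate is unbiased. The shifts in steps 2 and 3 are conditional on an unlucky allocation, and the 2.6 to 3.2 mmHg figure is the boundary case.
- **Power.** A reader might put SD 9.4 at both visits with ρ = 0.5 and obtain about 61% for the rule against 72% for ANCOVA. Most of the fall from 90% to 61% comes from replacing the planning SD, not from the choice of test. Moreover, if the change SD of 6.50 and visit SDs of 7.8 to 9.4 both held, ρ = 1−42.3/(2×SD²) would be about 0.65 to 0.76. There the gain at 9 mmHg is only some 2 to 4 points and the limit shift about 1.5 to 1.8 mmHg.
- **The criterion.** The protocol names no baseline significance test, so p>0.05 is only one reading; similarity could be judged by the size of the difference.
- **Missing detail.** Which characteristics trigger ANCOVA and which covariates enter could properly sit in a SAP that is not shown, so their absence is not the point.
- **Unequal variances.** The unequal planning SDs raise a different question from whether to adjust.

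What the reply does not rescue is the rule itself. The protocol states it and nothing else in the protocol overrides it. In every scenario run, ANCOVA was at least as powerful.

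**Conclusion.** The point holds as a matter of efficiency and conditional accuracy. The rule should be changed, but it does not make the trial's test invalid.

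Against the rule with change scores, adjusting in every case gains about 1 to 7 points of power at 9 mmHg and about 2 to 15 points at 5 mmHg. It also removes a shift that is typically about 1 mmHg and about 3 mmHg at the limit of what would pass as similar (ρ = 0.5). For scale, the planned effect is 9 mmHg.

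The sizes rest on a correlation the protocol does not give, on p>0.05 as the meaning of similar, and on SDs borrowed from two cited trials, one of them in normotensive people. The direction does not rest on the particular correlation: across the whole range examined, ANCOVA does no worse.

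**What to change.** Replace the conditional rule in *Statistical analysis* with a single sentence:

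> The between-group difference in week-8 SBP is estimated by ANCOVA with arm and baseline SBP, whatever the observed baseline balance.

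Use the same model for DBP, HR, grip strength and SMM, each with its own baseline value. With baseline in the model, analysing change or the week-8 value gives the same treatment estimate, so the ambiguity about which is compared disappears too. Baseline tables can stay as description but should not select the test.

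The cost is a wording change. Baseline values are already measured and ANCOVA is already in the plan, so no extra participants, visits or data are needed.

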**Feasibility of protocol**

Base on year 2019, number of elderly patients in Comprehensive Geriatrics Clinic at King Chulalongkorn Memorial Hospital is about 100 patients per month. Total sample size that planned to be enrolled in this study is 36. So, It has a high chance of being successfully completed.

**Ethical consideration**

Respect of person: All participants enrolled in this study will be well informed regarding the methods, aims and possible side effects of treatments. All participants will voluntarily provide their informed consent without feeling any pressure and can withdraw at any time. All information provided from participants is treated as confidential and will not be released by the researcher to a third party.

Beneficence/Non-maleficence: Isometric handgrip exercise is reported to be an alternative and effective exercise in reducing blood pressure. No serious side effects or complications from isometric handgrip exercise was reported in the literature. Although researcher will try to protect participants from any harm and treat if it occurs.

Justice: This study has clear inclusion and exclusion criteria for participation.

**Expected benefits gain**

If our protocol for home-based isometric exercise using commercial available device could result in blood pressure reduction in hypertensive elderly adults, it would be an alternative or add-on exercise that can help in blood pressure management in patients who are unable to perform aerobic exercise.

**Timeline**

Jan-May 2020 formulate the study protocol and applying for funding from grants for research and approval of Institutional Review Board of the Faculty of Medicine, Chulalongkorn University

June 2020 – June 2021 start recruiting participant after being approved and conduct the study

July-Dec 2021 analysis and conclusion of the study

